### This Study

This study seeks to investigate the long-term effects of meditation practice on quality of life and well-being in current ecological contexts through longitudinal examination of a cohort of beginner meditators who intend to continue practicing over one year. Specifically, this study aims to estimate the effectiveness of regular meditation practice after initial instruction for promoting quality of life (Aim 1, primary outcome) and mental well-being (Aim 2). We hypothesize that the amount of regular meditation practice during approximately the first year after initial instruction will predict practitioners’ quality of life, such that more regular practice predicts greater quality of life (Hypothesis 1). We also hypothesize that the amount of regular meditation practice during approximately the first year after initial instruction will predict practitioners’ mental well-being, such that more regular meditation will predict greater mental well-being (Hypothesis 2).

The study further aims to test whether the meditation tradition being secular or spiritual moderates any effects on quality of life (Aim 3). We hypothesize that whether participants’ meditation practice is predominantly secular or includes engagement with spiritual practices will moderate any effects on quality of life (Hypothesis 3, nondirectional). We further aim to test whether the meditation practice being secular or spiritual moderates any effects on mental well-being (Aim 4). Mental well-being captures the flourishing spectrum of mental health, and there may be moderation effects detectable in this domain that would not be evident for quality of life [33], either due to a lack of effect or because those relationships are obscured by potential ceiling effects in negatively worded quality of life measures. We hypothesize that whether the meditation tradition is secular or spiritual will moderate any effects on mental well-being (Hypothesis 4, nondirectional).

The study also aims to explore the cost-effectiveness of regular meditation practice on quality of life (Aim 5). Given that this is a cohort study and we will not have a control group as we would in an RCT, we will conduct an exploratory economic analysis using a comparator group of those not continuing with meditation compared to those that are, accounting for confounding factors.

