Finally, the study aims to document the incidence and impact on daily function of any challenging, difficult, or distressing meditation-related experiences (Aim 6). Meditation-related adverse effects (MRAEs) will be defined as any challenging, difficult, or distressing meditation-related experiences that impact everyday functioning. Our aims, hypotheses, and possible interpretations are summarized in Table 1 below.

**Table 1. T1:** Protocol Design table.

Question	Hypothesis	Sampling plan (eg, power analysis)	Analysis plan	Interpretation given to different outcomes
Does regular meditation practice after initial instruction increase quality of life?	The amount of meditation practice during approximately the first year predicts practitioners’ quality of life, such that a greater amount leads to greater quality of life.	A total number of 522 gives 95% power to detect the variance in quality of life (EQ-HWB-9^a^) explained by monthly meditation practice observed in linear mixed model analysis, at a 2-tailed significance level of 0.05, accounting for an estimated 20% loss to follow-up.	Linear mixed model of the fixed effect of the amount of meditation in the past month on quality of life in the past week (EQ-HWB-9), controlling for the confounding factors of age, caring status, education, mental health diagnosis, commitment to meditation, and membership of a practice support community at baseline.	A positive/negative and statistically significant association between the amount of meditation in the past month on quality of life and in the past week will suggest that regular meditation practice after initial instruction increases/decreases quality of life in a linear fashion. A nonsignificant association will suggest an absence of evidence for either of these effects.

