Does regular meditation practice after initial instruction increase mental well-being?	The amount of meditation practice during approximately the first year predicts practitioners’ mental well-being, such that a greater amount leads to greater mental well-being.	A number of 242 gives 95% power to detect the variance in mental well-being (SWEMWBS^b^) explained by monthly meditation practice observed in linear mixed model analysis, at a 2-tailed significance level of 0.05, accounting for an estimated 20% loss to follow-up.	Linear mixed model of the fixed effect of the amount of meditation in the past month on mental well-being in the past 2 weeks (SWEMWBS), controlling for the confounding factors of age, caring status, education, mental health diagnosis, commitment to meditation, and membership of a practice support community at baseline.	A positive/negative and statistically significant association between the amount of meditation in the past month on mental well-being in the past 2 weeks will suggest that regular meditation practice after initial instruction increases/decreases mental well-being in a linear fashion. A nonsignificant association will suggest an absence of evidence for this.
Is the effect of continued meditation practice after initial instruction on quality of life moderated by whether a practitioner’s meditation tradition is spiritual or secular?	Whether the meditation tradition is secular or spiritual will moderate any effects on quality of life (nondirectional)	Sampling plan follows hypothesis 1, with an additional 20%, n=627, powered to detect effect of f^2^=0.0318	Linear mixed model of the fixed effect of the amount of meditation in the past month and the interaction effect of tradition spirituality on quality of life in the past week (EQ-HWB-9), controlling for the confounding factors of age, caring status, education, mental health diagnosis, commitment to meditation, and membership of a practice support community at baseline.	A positive/negative statistically significant beta coefficient for this interaction will indicate that regular meditation practice within a spiritual tradition will have a larger/smaller effect on quality of life than practicing within a secular tradition. A nonsignificant association will suggest absence of evidence for this.

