Quality of life will be assessed at baseline, monthly, and one year, using the 9-item EQ Health and Wellbeing (EQ-HWB-9) instrument [58]. The EQ-HWB-9 captures mental (eg, depression and cognition), physical (eg, pain), and social (eg, loneliness) aspects of quality of life for the past 7 days, on a 5-point Likert scale from 1 (No difficulty) to 5 (Unable). Previous responsiveness to change analysis indicates that the EQ-HWB-9 detects meaningful changes in both mental and physical health measures [59]. This will be our primary outcome. The EQ-HWB-9 also allows for the calculation of quality-adjusted life years (QALYs), a standard measurement in health decision-making, and thus allows for the comparison of both effectiveness and cost-effectiveness with many other interventions and standard treatments [60].

Mental well-being will be assessed at baseline, monthly, and one year using the Short Warwick-Edinburgh Mental Well-Being Scale (SWEMWBS) [61,62]. The SWEMWBS includes 7 items that assess mental well-being over the past 2 weeks, on a 5-point Likert scale from 1 (None of the time) to 5 (All of the time). This will be our secondary outcome. The items in the SWEMWBS are positively worded (eg, “I’ve been feeling optimistic about the future”) and aim to capture variation in the flourishing side of the well-being spectrum, which will supplement detailed variation in the quality of life deficits captured by the EQ-HWB-9. Previous analyses of responsiveness to change indicate that the SWEMWBS detects individually meaningful improvement across a variety of mental health measures [63].

MRAEs will be measured at baseline, one year, and monthly, using the 3-item MRAEs measures [42]. The first item asks participants to indicate the frequency of any challenging, difficult, or distressing meditation-related experiences, with options ranging from “never” to “frequently.” The second item assesses the level of impairment caused by these experiences on the participant’s ability to function, with options ranging from “not at all” to “severely.” The third item asks about the duration of the impairment, with options ranging from “1 day or less” to “1 year or longer.”

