### Sampling Plan

#### Hypothesis 1

Sample size calculation for quality of life measured by the EQ-HWB-9 using repeated measures linear mixed modeling assumes three groups will be assessed with (1) low, (2) medium, and (3) high regular meditation dosage. Given the limited research on the effects of long-term regular meditation practice, calculating power is challenging. We have therefore used conservative power calculations that may err on the side of underestimating the power of our primary analysis but allow for use of the effect information and analytic tools that are available. We have conducted power analysis using 3 levels of variation in the predictor of monthly meditation amount, rather than the continuous variable we plan to use in our final analysis. This is to allow for the use of an analytic power calculation method for our repeated measures design, rather than simulation measures, which would be highly speculative with the limited real and independent data available for our outcome measure [64]. Ten measurement time points were also used, rather than the 12 that will be included in our analysis, as this is the maximum for GLIMMPSE (University of Florida and University of Colorado Denver) power analysis software [65].

Sample size calculation for quality of life measured by the EQ-HWB-9 using repeated measures linear mixed modeling assumes three groups will be assessed with (1) low, (2) medium, and (3) high regular meditation dosage. No increase in EQ-HWB-9 scores was predicted for the low meditation group [58]. For the high meditation group, we estimate a stepwise increase to a minimum of a 2.25-point EQ-HWB-9 increase (out of a possible 9‐45 points) from baseline to time point 5, corresponding to the change in EQ-HWB-9 from baseline to 6 months associated with improvement in mental health in a validation of the EQ-HWB-9 sensitivity to change [59]. We then predict a further 2.25-point increase to time point 10, for a total increase of 4.5 points. For the moderate meditation group, stepwise improvement was predicted with a minimum of a 2.25-point EQ-HWB-9 increase from baseline to time point 10. Baseline EQ-HWB-9 is set at 19.6, with an SD of 7.0, as per our nationally representative surveys [66]. Using GLIMMPSE [65] with 95% power and 0.05 2-tailed type 1 error rate, sample size was calculated at 435 participants. We estimated a 20% loss to follow-up over one year, bringing the sample size required to 522 participants.

#### Hypothesis 2

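### The EQ-HWB-9 is described so that a higher score is worse, but the Hypothesis 1 planning trajectories count a rise as improvement; the score's direction must be fixed before the Table 1 sign rules are applied

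*Protocol article*

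**What the plan says.** **Scoring (Measures).** The EQ-HWB-9 is rated "on a 5-point Likert scale from 1 (No difficulty) to 5 (Unable"; the lowest response is the best state and the highest the worst. The same section contrasts it with the positively worded SWEMWBS, "which will supplement detailed variation in the quality of life deficits captured by the EQ-HWB-9". The introduction (This Study) also refers to "potential ceiling effects in negatively worded quality of life measures".

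**Planning values (Sampling Plan, Hypothesis 1).** The possible range is 9 to 45, the range of a sum of nine items scored 1 to 5. "Baseline EQ-HWB-9 is set at 19.6, with an SD of 7.0", a value attributed to nationally representative surveys. For the high-dose group, "we estimate a stepwise increase to a minimum of a 2.25-point EQ-HWB-9 increase" by time point 5, then a further 2.25 points by time point 10. The moderate group's improvement is also entered as a rise of 2.25 points. The low-dose group is given no rise. The 2.25 points are tied to better mental health in a validation study.

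**Interpretation (Table 1).** For Hypothesis 1, "A positive/negative and statistically significant association between the amount of meditation in the past month on quality of life" is taken, according to its sign, to mean that practice raises or lowers quality of life. For Hypothesis 3, the sign of the interaction's beta coefficient decides whether "regular meditation practice within a spiritual tradition will have a larger/smaller effect on quality of life than practicing within a secular tradition".

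**Model (Analysis Plan).** The outcome is named as quality of life by the EQ-HWB-9. Whether this is the raw sum, a reversed sum or an index value is not said. Index values appear only for the QALYs of Aim 5.

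**The concern.** Two statements about the primary outcome point in opposite directions. By the item anchors, a higher EQ-HWB-9 score means more difficulty. By the planning trajectories, a higher score means improvement. Nothing in the article connects the two by a reversal.

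What is at stake is the reading of the result. Table 1 fixes in advance what a positive and a negative finding will mean, and it uses the same form of words for the EQ-HWB-9 and the SWEMWBS. The SWEMWBS is positively worded and runs from none to all of the time, so higher is better. If the EQ-HWB-9 is modelled as described, the same sign means opposite things for the primary and the secondary outcome. A beneficial association could then be labelled harmful, or a harmful one beneficial. Settling the direction only after the coefficient is known would weaken a preregistered decision rule.

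**Working it through.** **Inputs.** From Measures: nine items, each 1 (best) to 5 (worst). From Sampling Plan, Hypothesis 1: range 9 to 45; baseline 19.6; SD 7.0; changes of +2.25 (moderate) and +4.5 (high) by time point 10; alpha 0.05 two-tailed; 95% power; 435 participants, 522 after 20% loss.

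**1. The plan's own sample size.** 435 × 1.2 = 522, as stated. The 435 itself can be neither confirmed nor refuted, because the article gives no within-person correlation. A Hotelling-Lawley approximation of the group-by-time test (three equal groups, ten time points, SD 7.0) gives 93 to 303 for compound symmetry with correlation 0.8 down to 0.3. It gives about 160 to 650 for the decaying correlations tried. The combined range includes 435.

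**2. What the trajectories mean on the scoring described.**
- Baseline: 19.6/9 = 2.18 per item; (19.6 − 9)/36 = 29% of the way from best to worst.
- High-dose group at time point 10: 19.6 + 4.5 = 24.1; 24.1/9 = 2.68 per item; (24.1 − 9)/36 = 42% of the way to worst.
- Size of the move: 4.5/7.0 = 0.64 SD, towards more difficulty.

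So what is called improvement is a deterioration on the scale that Measures describes.

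**3. Whether an unstated reversal rescues the text.** The reversed sum is 54 minus the raw sum, with the same 9 to 45 range. If 19.6 were already reversed, the raw baseline would be 54 − 19.6 = 34.4. That is 34.4/9 = 3.82 of 5 per item, or (34.4 − 9)/36 = 71% of the way to worst. It is not credible as the average of a nationally representative sample, and it sits badly with the article's own worry about ceiling effects.

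| Reading of the score | Baseline 19.6 | Rises of 2.25 and 4.5 as improvement |
|---|---|---|
| Raw sum (higher = worse) | fits | wrong direction |
| Reversed sum (higher = better) | implausible (raw 34.4) | fits |

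Neither reading makes both inputs right.

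**4. Consistent versions.**
- Raw sum: high-dose 19.6 − 4.5 = 15.1; moderate 19.6 − 2.25 = 17.35.
- Reversed sum: baseline 34.4; high-dose 34.4 + 4.5 = 38.9; moderate 34.4 + 2.25 = 36.65.

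**5. Effect on sample size.** With the changes entered as decreases, the approximation gives the same N under every correlation tried. For example, it gives 219 and 219 at compound symmetry 0.5, and 441 and 441 at one decaying pattern starting from 0.5. This is expected: the test statistic is quadratic in the mean differences, so flipping their sign leaves it unchanged.

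**6. Effect on the Table 1 rules, if the raw sum is modelled.** Benefit gives a negative coefficient for practice. A positive interaction shifts the slope in spiritual practitioners towards worse scores, the opposite of what the Hypothesis 3 cell conveys. For the SWEMWBS the rules read correctly.

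**The case against.** The best defence is that Table 1's Hypothesis 1 cell speaks of the construct. A positive association between practice and quality of life does mean that quality of life is higher with more practice, however the instrument is coded. No passage says that the raw sum enters the model, and a reversed sum has the same range. The trajectories and the interpretation rules all treat higher as better, which would fit a recoding step that a journal article leaves to a fuller document. The authors plainly know that the items are negatively worded. The implausibility of a reversed 19.6 is an inference about a survey that is not shown. Nothing in the design, data or sample size changes.

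Much of this stands. A reader might infer that the primary result is bound to be reported with the wrong sign, or that the sample size is wrong. The documents support neither: the coding of the modelled score is not stated, and a two-tailed calculation does not depend on sign.

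What does not stand is that this is only an omitted detail. The article itself states the item direction, range, baseline and expected change, and these cannot all hold together. An intended recoding would leave the baseline in need of correction. The Hypothesis 3 rule is also tied explicitly to the sign of a coefficient, so it needs a defined score direction.

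**Conclusion.** The point holds as an internal contradiction about the direction of the primary outcome. As written, the Hypothesis 1 planning text moves the high-dose group 4.5 points (0.64 SD) towards worse quality of life and calls it improvement. It needs correcting whether the score is raw or reversed.

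The consequence for interpretation is conditional. If the score as described enters the model, the Hypothesis 3 rule gives the wrong reading. The Hypothesis 1 rule does too if its positive/negative wording is applied to the EQ-HWB-9 coefficient. If the score is recoded first, both rules read correctly and only the planning baseline is at fault. Hypotheses 2 and 4 are unaffected, and 435/522 does not change for this reason.

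The conclusion rests on the item anchors and range as printed, and on the judgement that a general-population average of about 3.8 of 5 on difficulty is implausible. Because it concerns the primary outcome and its prespecified interpretation, it should be settled before analysis.

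**What to change.** Name the primary EQ-HWB-9 score and its direction once, in Measures, and carry it through. Either choice resolves the point:

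- **Reverse-scored:** 54 minus the 9 to 45 sum, higher = better. The planning baseline becomes 34.4, rising to 36.65 (moderate) and 38.9 (high). The Table 1 signs for Hypotheses 1 and 3 then stand.
- **Raw sum:** higher = worse. The baseline stays at 19.6, falling to 17.35 (moderate) and 15.1 (high). The Hypothesis 1 and 3 cells are reworded so that a negative coefficient for practice is benefit, and the interaction sign is read accordingly.

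In both cases, state in the Analysis Plan which score is modelled and use the same direction in all outputs. Reverse scoring has the advantage that the EQ-HWB-9 and the SWEMWBS run the same way. The cost is a few words in Measures, Sampling Plan, Analysis Plan and, for the raw sum, Table 1. It needs no new data and no change in sample size. With results expected in January 2028, it can be recorded as a dated clarification before any outcome analysis.
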